## Abstract

**Background:**

Knee osteoarthritis (KOA) is commonly seen and has a high occurrence in the middle-aged and elderly. It is characterized by the degeneration and secondary bone hyperplasia of the articular cartilage; the pathologic changes are irreversible. Therefore, treatment of KOA is mainly focused on relieving pain, reducing inflammation, improving or restoring joint function, delaying disease progression, and increasing quality of life. Crossbow needle therapy of the Miao ethnic minority group is intended for KOA treatment and has been widely used. Studies of small sample size have seen significant improvement on pain relief, stiffness, and joint function.

**Methods/design:**

The trial is a randomized, multicenter, parallel, non-inferiority study. Three hundred and six patients will be randomly assigned to a crossbow needle group (*n* = 153) and an acupuncture group (*n* = 153). Patients in each group will receive treatment every other day, three times a week, 20 times in total. Follow-up will be conducted 15 days and 30 days after treatment. The primary outcome will be the Western Ontario and McMaster Osteoarthritis Index (WOMAC) score at baseline, the end of treatment, first follow-up, and second follow-up. The secondary outcomes will include Lysholm knee score, Japanese Orthopedic Association (JOA) knee score, visual analogue scale (VAS), and the MOS 36-item short-form health survey (SF-36).

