### Sample size

The trial is designed to determine the efficacy of crossbow needle therapy on KOA and prove that its clinical efficacy is not inferior to normal acupuncture therapy; therefore, we chose a non-inferiority trial design [21]. Sample size calculation is based on the formula $$ n=2{\left[\frac{\left(\mu \alpha +\mu \beta \right)s}{\delta}\right]}^2 $$, in which μα and μβ are constants and *s* is the combined standard deviation. We set *α* at 0.05 (one-sided), *β* at 0.10, *δ* at 1.5, and *s* at 4.0 (*δ* and *s* based on expert consensus to determine the formula parameters, but not clear as currently), with *μα = μ*_0.05_ = 1.645 and *μβ = μ*_0.10_ = 1.282. After calculation, the sample size of each group should be around 122. Assuming a 20% dropout rate, each group needs at least 153 patients; 306 patients will be recruited in the trial.

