### Outcome measures

#### Primary outcome measures

We will use the Western Ontario and McMaster Universities Osteoarthritis Index (WOMAC) as the primary outcome measure [26]. The WOMAC is a questionnaire composed of 24 questions to assess physical functional disability. It was developed for patients with osteoarthritis of the hip or knee and measure three subscales: pain; stiffness; and physical function. Higher scores indicate more severe symptoms or physical disability. The Nimodipine method will be applied to calculate the efficacy.

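### No WOMAC measure or visit is named as the deciding primary comparison, so the stated 5% error rate and 90% power attach to no identified test

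*Protocol article*

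**What the plan says.** The Methods/design part of the abstract states the primary outcome as "WOMAC) score at baseline, the end of treatment, first follow-up, and second follow-up". The two follow-up visits are 15 and 30 days after treatment.

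The section on primary outcome measures names WOMAC "as the primary outcome measure" and gives no visit. The trial registration table (Table 1) also gives WOMAC with no visit. The outcome section describes the instrument as one that "measure three subscales: pain; stiffness; and physical function", and does not say whether the total, a change from baseline or a subscale is compared. It closes with a further expression of the outcome: "The Nimodipine method will be applied to calculate the efficacy". The method is not defined.

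The Sample size section explains the design ("therefore, we chose a non-inferiority trial design") and its inputs: "We set *α* at 0.05 (one-sided), *β* at 0.10, *δ* at 1.5, and *s* at 4.0". It describes δ and s as "based on expert consensus to determine the formula parameters, but not clear as currently" and does not say to which WOMAC measure or visit they belong. The result is: "After calculation, the sample size of each group should be around 122". An allowance of 20% for dropout raises this to 153 per group, 306 in all.

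The Statistical analysis section makes every test one-sided at p < 0.05 and lets the data distribution decide among Wilcoxon, t test and analysis of variance. It ties no test to a visit or measure and sets no order among tests. It promises an analysis plan before database lock.

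**The concern.** A one-sided α of 5% and a power of 90% are properties of a specific test. Here the sample size is built for one two-group mean difference, while the primary outcome is spread over several visits and expressed in two ways: as a score and by the Nimodipine method. A reader cannot tell which comparison the trial was sized for or which one will decide it.

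This matters more under non-inferiority than under superiority, because a margin of 1.5 has meaning only on a named measure. If the choice of visit or measure is left open until results are known, the claim could rest on whichever one passes. If success is needed throughout, the trial is smaller than its stated power implies. The trial is already recruiting and patients are not blinded, which adds to the case for settling the choice soon.

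**Working it through.** **Inputs from the protocol.** One-sided α = 0.05 (1.645), β = 0.10 (1.282), δ = 1.5, s = 4.0, dropout 20%, allocation 1:1 (Sample size; Randomization and blinding). Three post-baseline visits (abstract). I read δ as the non-inferiority margin with a true difference of zero, which is what the formula implies.

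**Step 1: the plan's own figure.**

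n = 2[(1.645 + 1.282) × 4.0 / 1.5]² = 2 × (7.805)² = 121.85, rounded up to 122 per group.

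122 / 0.8 = 152.5, rounded up to 153 per group, or 306 in total.

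Power at 122 per group: the standard error is 4.0 × √(2/122) = 0.512, so 1.5 / 0.512 = 2.929 and Φ(2.929 − 1.645) = 90.0%.

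The stated 122, 153 and 306 all reproduce, for one comparison.

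**Step 2: three visits under each possible success rule.** The protocol states no rule, so I take both. For the error rate, the true difference lies exactly at the margin at all three visits. For power, it is zero at all three, with δ = 1.5 and s = 4.0 applying at each. If the three tests were independent:

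- Any one visit suffices: error = 1 − 0.95³ = 14.3%.
- All three required: power = 0.9004³ = 73.0%.

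Repeated measurements on the same patients will be correlated, and the documents give no correlation. I therefore simulated three normal test statistics with equal pairwise correlation (1,000,000 draws per row, threshold 1.645):

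| Assumed correlation | Error if any visit suffices | Power if all three required |
|---|---|---|
| 0 | 14.3% | 73.1% |
| 0.3 | 13.0% | 75.9% |
| 0.5 | 11.9% | 78.2% |
| 0.7 | 10.3% | 81.1% |
| 0.8 | 9.2% | 82.9% |
| 0.9 | 8.0% | 85.1% |

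Only at a correlation of 1 would the three visits act as one test and both stated figures hold whichever rule applied.

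**Step 3: what a remedy would need.**

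- One named contrast: 122 per group, 153 after dropout, with 5% error and 90% power, provided that 1.5 and 4.0 belong to that measure.
- Three visits with any one sufficient, each tested at 0.05/3 (Bonferroni): 166 per group; 166 / 0.8 = 207.5, rounded up to 208, or 416 in total. At 122 per group, the power of each single test would be 78.8%.
- Three visits with all required: the error rate stays within 5%, and power is as in the last column above.

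**The case against.** The strongest reply is that this is a condensed article with an analysis plan still to come, and a success rule across visits is something such a plan commonly supplies. The abstract's list can be read as the WOMAC assessment schedule, in which baseline belongs because any change score needs it. The word score is singular, which suggests one measure.

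Much of this stands. Listing baseline is a small fault in itself. The absence of a multiplicity rule from the article would not be a finding alone. The protocol does not say that success at any one visit is enough, so the 8% to 14% is conditional on that rule, just as the 73% to 85% is conditional on the opposite one.

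The reply does not remove the core. The article does more than leave a detail out: it gives primary status to several visits, adds an undefined efficacy measure to the same outcome, and commits to one α, one δ, one s and one power. An analysis plan can specify models, but the comparison to which a margin and a sample size refer should be recognisable in the protocol. Read purely as a schedule, the abstract's list still leaves no deciding visit anywhere in the document.

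A reader might also infer two stronger points that the text does not support:

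- **Twelve primary tests (total and three subscales at three visits).** The outcome section mentions the subscales only as the structure of the questionnaire. Nothing says each is tested as primary. Three visits is the count that the text supports.
- **A measurable power loss from the Nimodipine method.** The method is undefined here. Treating it as a percentage or graded response, and putting a figure on the loss, would need a definition and baseline values from outside the documents. What can be said is that its relation to the mean difference in the Sample size section is not stated.

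**Conclusion.** The point holds in this form: the primary endpoint is badly fixed, because no deciding visit or WOMAC measure is identified and the undefined Nimodipine measure is not linked to the sample size. The departure from the stated design is an error of 8% to 14% instead of 5%, or power of 73% to 85% instead of 90%, depending on which success rule was intended. Both ranges rest on assumed equal correlations from 0.9 down to 0 for the error and from 0 up to 0.9 for power, and on the same δ and s at every visit.

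It should not be read as saying that the sample size is miscalculated; the calculation is exact for one comparison. Nor do the documents show that 1.5 and 4.0 belong to the WOMAC total at end of treatment. The Sample size section names no measure and itself calls the parameters unclear.

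**What to change.** Before database lock and before any unblinded data are seen:

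1. Name one WOMAC measure at one post-baseline visit as the single primary non-inferiority contrast. The total score at end of treatment, as a baseline-adjusted mean difference in points, is one example. The choice is the investigators' to justify.
2. State that δ = 1.5 and s = 4.0 refer to that measure, or restate the margin, SD and power if they do not.
3. Treat baseline WOMAC as a covariate.
4. Make the other visits, the subscales and the Nimodipine measure secondary, and define the last.
5. Use the same wording in the abstract, Table 1 and the section on primary outcome measures.

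If 1.5 and 4.0 do describe the chosen measure, the cost is wording only and 153 per group stands. If they do not, the cost could be larger: n is proportional to s², so twice the SD with the same margin would need four times the patients. The downside in either case is that the other visits and the Nimodipine measure lose confirmatory status. Keeping three visits with any one sufficient would instead need 208 per group (416 in total) under Bonferroni.

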**Discussion:**

The results of the trial will compare the efficacy on KOA between crossbow needle group and acupuncture group and will be expected to make a systematic and objective evaluation of crossbow needle therapy.

**Trial registration:**

ChiCTR, ChiCTR-INR-16008032. Registered on 12 March 2016.

**Electronic supplementary material:**

The online version of this article (10.1186/s13063-018-2730-4) contains supplementary material, which is available to authorized users.

## Background

Knee osteoarthritis (KOA) is a common chronic progressive disease characterized by the degeneration and secondary bone hyperplasia of the knee articular cartilage. It is associated with many factors such as age, body mass index, sex, inflammation, long-term improper exercise, and heredity. Its main signs and symptoms include arthralgia, ankylosis, and functional disorders. Together with obesity, KOA is believed to affect mostly Americans aged 50–84 years [1]. Among people aged under 65 years, more than half have reported three or more years of KOA [2]. In China, KOA morbidity varies among areas, but overall is rising every year. It was estimated that 200,000 patients per year would receive joint replacement [3]. With the aging population, KOA is now a major health risk for middle-aged and elderly people.

Damages on articular cartilage are often irreversible. Neither drug therapy nor surgical treatment can stop the progression of KOA, so treatment of KOA is mainly focused on relieving, reducing inflammation, improving or restoring joint function, delaying disease progression, and increasing quality of life [4]. In western medicine, drug therapy and surgical treatment are the two major interventions of KOA. Drug therapy takes effect very soon, but it always comes with certain side effects and gastrointestinal adverse reaction. Surgical treatment tends to be expensive and is often accompanied by contraindications and complications, limiting its wide application. Back in 1996, KOA was confirmed to be one of the 64 indications of acupuncture therapy in Milan, Italy [5]. Acupuncture is a physical therapy and has no side or toxic effects. Many clinical trials have confirmed its effect on relieving pain and improving joint function in KOA treatment [6–10].

With the support of ethnic minority medicine by the Chinese government, many unique therapies have been discovered and applied because of their remarkable therapeutic effect. Of the 40-odd external therapies in the Miao ethnic minority group, crossbow needle therapy has extremely wide application. It combines needling treatment with transdermal drug administration through the needle and is a broad-spectrum therapy. In Miao medicine, the crossbow needle is traditionally applied to treat cold-bone wind syndrome and cat-head wind syndrome [11–14], while in modern clinical medicine, it is used to treat KOA more often. So far, clinical studies of crossbow needle therapy are all small single-center trials [15–18], which lack clinical evidence and are not enough to make a correct and accurate evaluation.

Thus, we designed this multicenter randomized controlled trial to assess the efficacy of crossbow needle therapy on KOA, in the hope of obtaining replicable evidence that could rank high on the clinical evidence hierarchy, providing further guidance for its development and application.

## Methods/design

### Study design and setting

This is a parallel, non-inferiority, randomized controlled clinical trial to compare the effect of crossbow needle therapy and regular acupuncture therapy on KOA patients. The patients will be enrolled among outpatients and inpatients from the acupuncture departments of No. 1 Affiliated Hospital of Guiyang University of Chinese Medicine, No. 2 Affiliated Hospital of Guiyang University of Chinese Medicine, and Chinese Medicine Hospital of Qiandongnan Miao and Dong Autonomous Prefecture. Eligible patients will be randomly assigned to a crossbow needle group and an acupuncture group in a 1:1 ratio. All items from the World Health Organization Trial Registration Data Set are shown in Table 1. The study flowchart is provided in Fig. 1. A Standard Protocol Items: Recommendations for Interventional Trials (SPIRIT) checklist and figure are provided respectively in Additional file 1 and Fig. 2.

**Table 1 Tab1:** All items from the World Health Organization Trial Registration Data Set (SPIRIT checklist, item 2b)

Data category	Information
Primary registry and trial identifying number	http://www.chictr.org.cn; ChiCTR-INR-16008032
Date of registration in primary registry	12 March 2016
Secondary identifying numbers	–
Source(s) of monetary or material support	Special research project of traditional Chinese medicine in 2015 (201507006–01)
Primary sponsor	Institute of Basic Research In Clinical Medicine, China Academy of Chinese Medical Sciences
Secondary sponsor(s)	–
Contact for public queries	[name]; [contact]
Contact for scientific queries	[name], Institute of Basic Research In Clinical Medicine, China Academy of Chinese Medical Sciences, Beijing 100,700, China.
Public title	Miao medicine in knee osteoarthritis study
Scientific title	Crossbow needle therapy of the Miao ethnic minority group on knee osteoarthritis: study protocol for a multicenter, randomized controlled trial
Countries of recruitment	China
Health condition(s) or problem(s) studied	knee osteoarthritis, pain/ankylosis/joint function disturbance
Intervention(s)	Crossbow needle therapy of the Miao ethnic minority group
Key inclusion and exclusion criteria	*Inclusion criteria* Patients who meet all of the following criteria will be enrolled in the trial: (1) aged 40–75 years; (2) meeting the above diagnostic criteria 1 and 2 (patients graded 1, 2, or 3 osteoarthritis by Kellgren-Lawrecne scale); (3) meeting the above diagnostic criteria 1, 4, 5, and 6; (4) the more affected side to be included when KOA is present on both sides; (5) no intervention performed 1 week before enrollment; (6) aware of all the tasks involved in the trial and prepared to comply with treatment; (7) willingness to sign written informed consent. *Exclusion criteria* Patients who meet any of the following criteria will be excluded from the trial: (1) failed to meet the diagnostic criteria and inclusion criteria; (2) women in pregnancy or lactation; (3) susceptible to allergy; (4) other knee disorders; (5) contusion or sprain in ankle or foot, or other disorders that affect normal walking; (6) ankle/foot deformity or pain; (7) skin disorders or deep swelling at the treated site; (8) other severe primary diseases or complications.
Study type	Multicenter prospective randomized trial
Date of first enrolment	13 April 2016
Target sample size	306
Recruitment status	Recruiting
Primary outcome(s)	The Western Ontario and McMaster Universities Osteoarthritis Index (WOMAC)
Key secondary outcomes	The visual analogue scale (VAS); the Japanese Orthopedic Association (JOA) score; the MOS 36-item short-form health survey (SF-36)

**Fig. 1 Fig1:**
[figure not shown]
*Flow chart* of the trial

**Fig. 2 Fig2:**
[figure not shown]
The SPIRIT figure. The schedule of enrollment, interventions, and assessments. WOMAC Western Ontario and McMaster Universities Osteoarthritis Index, SF-36 MOS 36-item short-form health survey, VAS visual analogue scale

### Study population

#### Diagnostic criteria

The diagnostic criteria [19] are:Frequent knee pain in the recent month;Osteophytes at the joint margin by X-ray;Diagnosis confirmed by joint fluid examination;Aged > 40 years;Morning stiffness < 30 min;Bony crepitus.

Those who meet 1 and 2, or 1, 3, 5, and 6, or 1, 4, 5, and 6 can be diagnosed with KOA. In terms of practical considerations, we will only recruit patients who meet 1 and 2, or 1, 4, 5, and 6.

#### Inclusion criteria

Patients who meet all of the following criteria will be enrolled in the trial:Aged 40–75 years;Meeting the above diagnostic criteria 1 and 2 (patients graded 1, 2, or 3 osteoarthritis by Kellgren-Lawrecne scale [20]);Meeting the above diagnostic criteria 1, 4,5, and 6;The more affected side to be included when KOA is present on both sides;No intervention performed one week before enrollment;Aware of all the tasks involved in the trial and prepared to comply with treatment;Willingness to sign written informed consent.

#### Exclusion criteria

Patients who meet any of the following criteria will be excluded from the trial:Failed to meet the diagnostic criteria and inclusion criteria;Women in pregnancy or lactation;Susceptible to allergy;Other knee disorders;Contusion or sprain in ankle or foot, or other disorders that affect normal walking;Ankle/foot deformity or pain;Skin disorders or deep swelling at the treated site;Other severe primary diseases or complications.

### Sample size

The trial is designed to determine the efficacy of crossbow needle therapy on KOA and prove that its clinical efficacy is not inferior to normal acupuncture therapy; therefore, we chose a non-inferiority trial design [21]. Sample size calculation is based on the formula $$ n=2{\left[\frac{\left(\mu \alpha +\mu \beta \right)s}{\delta}\right]}^2 $$, in which μα and μβ are constants and *s* is the combined standard deviation. We set *α* at 0.05 (one-sided), *β* at 0.10, *δ* at 1.5, and *s* at 4.0 (*δ* and *s* based on expert consensus to determine the formula parameters, but not clear as currently), with *μα = μ*_0.05_ = 1.645 and *μβ = μ*_0.10_ = 1.282. After calculation, the sample size of each group should be around 122. Assuming a 20% dropout rate, each group needs at least 153 patients; 306 patients will be recruited in the trial.

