#### Secondary outcome measures

The Lysholm knee score will be used to assess knee function of the patients. The score is rated 0–100, with 25 points attributed to pain, 15 to locking, 10 to swelling, 25 to instability, 10 to stair climbing, and 5 each to squatting, limp, and support.

The Japanese Orthopedic Association (JOA) score is a frequently used scale. It comprises ratings of pain (40 points), range of motion (20 points), gait (20 points), and activities of daily living (20 points). The JOA score will be used to assess the therapeutic effect, with a higher score indicating better effect.

The visual analogue scale (VAS) will be applied to evaluate the pain intensity of the patients. It is a standard tool in pain studies to measure pain intensity. The score is in the range of 0–100 (0 indicating no pain and 100 indicating the worst pain imaginable).

The MOS 36-item short-form health survey (SF-36) will be used to assess the patients’ living standard before and after treatment. The health survey consists of eight dimensions: physical function; role limitations due to physical problems; bodily pain; general health; vitality; social function; role limitations due to mental problems; and mental health. Higher scores represent better quality of life.

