### Statistical analysis

Data analysis will be conducted in accordance with the intention-to-treat principle. Missing data will be handled using linear mixed effects models. Statisticians and chief investigators will work out an analysis plan and related forms before database lock. The analysis will include case distribution, comparison of basic values, compliance, effectiveness, factors that influence efficacy, and safety. Statistical analysis will be conducted using SAS 9.2 (SAS Institute Inc., Cary, NC, USA). The Wilcoxon rank sum test, *t* test, or variance analysis will be performed for inter-group or intra-group comparison according to data distribution. The Wilcoxon rank sum test will be used to compare ranked data. The chi-square test will be applied to compare enumeration data. All tests will be one-sided. A *p* value < 0.05 will be considered statistically significant.

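### The stated aim of determining efficacy and the planned within-group significance tests go beyond what a two-arm, active-control, open trial can show; the conclusion should be limited to non-inferiority against acupuncture

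*Protocol article*

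**What the plan says.** Three parts of the protocol article bear on this.

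- **Aim.** The Sample size section gives two aims in one sentence: "The trial is designed to determine the efficacy of crossbow needle therapy on KOA and prove that its clinical efficacy is not inferior" to ordinary acupuncture. It then offers this as the reason for a non-inferiority design. The Background section names only the first aim: "we designed this multicenter randomized controlled trial to assess the efficacy of crossbow needle therapy on KOA".
- **Design.** Study design and setting describes a "non-inferiority, randomized controlled clinical trial to compare the effect of crossbow needle therapy and regular acupuncture therapy on KOA patients", with patients "randomly assigned to a crossbow needle group and an acupuncture group in a 1:1 ratio". There is no sham or untreated arm. Randomization and blinding says that patients are not blinded. The primary outcome, WOMAC, is a questionnaire.
- **Tests.** In the Statistical analysis section, a Wilcoxon test, a t test or "variance analysis will be performed for inter-group or intra-group comparison according to data distribution". The same section adds: "All tests will be one-sided", with significance at p < 0.05. It does not place the within-group tests below the between-group ones.

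On entry, both diagnostic routes in use require "Frequent knee pain in the recent month". In bilateral disease the worse knee is taken, and no treatment is allowed in the preceding week. No minimum WOMAC or VAS score is set. The SF-36 "will be used to assess the patients’ living standard before and after treatment"; this is context only, since it names no test.

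**The concern.** Change within one arm is a sum: any specific effect of the treatment, the natural course of symptoms, regression to the mean after selection on recent pain and the worse knee, and, in unblinded patients answering a questionnaire, expectation. Randomisation balances natural course and regression to the mean between arms, so the between-arm difference is protected from them. A within-arm test is not, and this design has no arm from which the non-specific part could be estimated.

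The protocol nevertheless states an absolute aim (efficacy of crossbow needle therapy) and lists a test that appears to answer it. What is at stake is how the result is read. A small p-value for improvement in the crossbow arm could be taken as meeting the stated aim, even if the non-inferiority comparison were inconclusive.

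**Working it through.** **1. The plan's own figure.** Inputs from the Sample size section: one-sided α 0.05 (1.645), β 0.10 (1.282), δ 1.5, s 4.0, dropout 20%.

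n = 2 × [(1.645 + 1.282) × 4.0 / 1.5]² = 121.85, so 122 per group. 122 / (1 − 0.20) = 152.5, so 153 per group and 306 in total. The stated figures reproduce. They rest only on the between-group contrast, and this point does not dispute them.

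**2. Length of observation.** 20 treatments at three per week take about 20 / 3 = 6.7 weeks. The last follow-up is 30 days (4.3 weeks) later, so a patient is observed for about 11 weeks. That leaves time for symptoms to vary without treatment.

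**3. How readily a within-arm test is significant with no specific effect.** Let m be the mean non-specific fall in an arm and SDc the SD of the change. For a one-sided test at 0.05 (normal approximation):

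P(significant) = Φ(m × √n / SDc − 1.645), with n = 122 and √122 = 11.045.

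The document gives neither m nor SDc, so both are assumptions. If s = 4.0 is the SD at each visit and r is the baseline to follow-up correlation, SDc = 4.0 × √(2(1 − r)). This is 4.0 at r = 0.5 and 5.66 at r = 0. The points are taken to be on the scale of δ and s.

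| Non-specific fall m | SDc = 4.0 | SDc = 5.66 |
|---|---|---|
| 0.25 | 17% | 12% |
| 0.5 | 40% | 25% |
| 1.0 | 87% | 62% |
| 1.5 (equal to δ) | 99% | 90% |

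Example: m = 1.0 and SDc = 4.0 give 1.0 × 11.045 / 4.0 = 2.761. Subtracting 1.645 leaves 1.116, and Φ(1.116) = 0.868.

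**4. Does non-inferiority supply the efficacy claim indirectly?** If the two therapies have equal specific effects, including zero in both, the non-inferiority test passes with probability Φ(1.5 / (4.0 × √(2/n)) − 1.645).

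- n = 122: Φ(2.929 − 1.645) = 90%.
- n = 153: Φ(3.280 − 1.645) = 95%.

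A pass is therefore evidence about crossbow needle therapy relative to acupuncture. To reach efficacy, one also needs a quantified effect of acupuncture over sham or no treatment, and a margin tied to it. The Background section asserts that acupuncture works but gives no effect size. The Sample size section bases δ and s on expert consensus and says they are not yet clear.

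**The case against.** The strongest reply is that the plan already rests on the between-arm comparison. The rest of the Sample size sentence leads directly to the choice of a non-inferiority design. Study design and setting gives the purpose as a comparison of the two therapies, the Discussion paragraph of the Abstract says the results will compare efficacy between the groups, and the sample size uses only the between-group contrast. The list of tests is generic, and an analysis plan is to be written before database lock. An active-control design without a sham arm is also a legitimate choice. All of this stands, and it rules out several stronger readings that a reader might infer:

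- **That the within-group tests are the intended basis of the efficacy conclusion.** No section says so. Nor does any section say that a within-arm result would replace a failed non-inferiority test.
- **That those tests measure only natural course and regression to the mean.** Within-arm change also contains any real treatment effect; the parts simply cannot be told apart.
- **That a substantial regression to the mean is established.** Recent frequent pain and choice of the worse knee make some plausible. Its size cannot be derived, because entry sets no WOMAC or VAS threshold and the Background section describes a chronic progressive disease.

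It is also fair to say that the table in the working shows only what a one-sample test with 122 patients will detect. At small shifts the chance of a significant result is modest, and the table does not estimate how likely a false claim is in this trial.

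The objection does not remove two things that are written down. The aim is worded as efficacy in the Background and Sample size sections, and significance tests within groups are planned at the same one-sided level as the randomised comparison. A later analysis plan can settle how change is reported, but the protocol has already specified testing it.

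**Conclusion.** The point holds in a limited form. The design supports a conclusion relative to acupuncture. It does not support a free-standing statement that crossbow needle therapy is efficacious, and the planned within-group tests cannot fill that gap. With no specific effect, 122 patients per arm and an SD of change of 4.0, a non-specific fall of 0.5, 1.0 or 1.5 points would give a significant within-arm result about 40%, 87% or 99% of the time. At 5.66, falls of 1.0 and 1.5 give 62% and 90%. These figures depend on assumed falls and assumed SDs of change, and they illustrate the problem rather than predict the result.

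The randomised comparison, the 122 / 153 / 306 sample size and the primary inference are not affected. This is a cheap improvement, not a flaw in the trial's main test.

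**What to change.** - **Background and Sample size sections:** word the objective and the permitted conclusion as non-inferiority of crossbow needle therapy to acupuncture in these patients.
- **Statistical analysis section:** replace the within-group significance tests with within-arm change from baseline, reported descriptively with its confidence interval, and say that it will not be used as evidence of efficacy.
- **Same section:** state that every efficacy statement rests on the randomised between-arm difference.

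The cost is a few sentences. No patients, visits or data are added, and the sample size stays as it is. The sponsor gives up an uncontrolled before-after p-value.
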